#### Biomechanical proprieties of plantar flexors

2.6.2

Muscle stiffness, as expressed by the shear modulus (*μ*, in Kpa), will be assessed during passive ankle joint mobilization and during MVC of PF (34). An Aixplorer^®^ ultrasound scanner (Supersonic Imagine, version 6.1, Aix-en-Provence, France) will be used in Shear Wave Elastography (SWE) mode (musculoskeletal preset, penetration mode, scale: 600 kPa) to quantify muscle stiffness in PF (GM, GL, and SOL). During the evaluations, two ultrasound probes will be used: probe 1 (4–15 MHz, SL15-4; SuperSonic Imagine, Aix-en-Provence, France) for the GM and GL, and probe 2 (2–10 MHz, SL10-2; SuperSonic Imagine, Aix-en-Provence, France) for the SOL. Acoustic gel will be used as an interface between the skin and the probe. For passive muscle stiffness evaluation, three positions will be identified: P0 = 0° (Neutral position), P1 = 10° and P2 = 20° (from neutral position to dorsiflexion). For each position, the SWE measurement will be conducted twice in predetermined regions, with the order randomized and a 1-min rest period between measurements. Regarding the active stiffness evaluation, the reference position will require the hips to be flexed at 45°, the knee on the paretic side to be fully extended, and the ankle on the paretic side to be positioned at 90°. The ankle joint’s axis will align with the dynamometer’s axis of rotation, and the foot will be securely fastened to the dynamometer platform. To ensure stability, additional attachments will be employed to secure the thigh and trunk to the isokinetic ergometer seat. Then, participants will receive instructions to perform two maximal isometric contractions (MVC) of PF. For submaximal contractions (30, 50, 70% of MVC), participants will receive immediate visual feedback on their %MVC torque to achieve the experimenter’s target %MVC torque. Once the desired torque level will be reached, an ultrasound image will be taken. For each MVC torque level, the SWE measurement will be performed twice in each muscle in a randomized order. Each trial will have a maximum duration of 5 s, and subjects will be allowed rest periods between trials. SWE measurement during passive and active conditions will be used for further analysis.

#### Structural parameters

2.6.3

Fascicle length, thickness and pennation angle will be assessed using the ultrasound scanner (Supersonic Imagine, version 6.1, Aix-en-Provence, France) in B-mode (echography mode). Muscle thickness will be determined as the distance between the superficial and deep aponeuroses of the GM muscle (35). Fascicle length will be calculated by extrapolating the intersection with both aponeuroses and measuring the distance between their respective intersection points (35). Pennation angle will be defined as the angle between the fascicle and the deep aponeurosis (35). Fascicle length and pennation angle will be measured for three fibers, and the average will be used for analysis. For each parameter, the average of three measurements will be used for further analysis.

#### Neuromuscular parameters

2.6.4

Peak force and rate of force development (RFD) will be evaluated using the BIODEX isokinetic device (Biodex 4 Medical Systems, Inc., Shirley, NY, United States) during MVC of PF. The peak force value from the two trials of MVC will be recorded (aPeak, N). The relative peak force (rPeak, N/kg) will be calculated by normalizing the peak force to the participant’s body mass (aPeak/BM, N/kg). The dynamometer signals will be stored offline for subsequent analysis. Early RFD will also be obtained from each MVC contraction onset to 50 ms (RFD50-100). Late RFD will be acquired from 100 to 200 ms (RFD100-200). All RFD will be calculated from the linear slop of the force – time curve (*Δ* force/Δ time). Finally, maximal activation will be evaluated using the Trigno Wireless Electromyography (EMG) system (Delsys, Inc., Boston, United States) during the MVC of PF. Four EMG sensors will be placed on the GM, GL, SOL, and tibialis anterior (TA) muscles. Before attaching the electrodes, the skin will be carefully prepared by shaving and cleaning it with an abrasive cleaner and alcohol swab to minimize impedance. EMG sensors will be positioned on each muscle’s belly, aligned parallel to the muscle fibers as recommended by SENIAM guidelines (36). The placement of EMG electrodes will be meticulously verified using ultrasound to ensure longitudinal alignment with the muscle fascicles and proper positioning away from neighboring muscles (37). EMG signal will also be recorded during passive evaluation.

### Data analysis

2.7

Data will be processed using MATLAB software (MATLAB R2024a, MathWorks, Natick, USA). Ultrasound images will be exported from Aixplorer’s software. Shear displacements will be calculated using a speckle-tracking algorithm. Tissue displacement maps will be used to calculate shear-wave velocity (SWV, m/s) in each pixel of the map. Then, the shear modulus (*μ*) will be calculated as follows:

$$\mu =\rho .SWV^{2},\mathrm{where}\;\rho \;\mathrm{is}\;\mathrm{the}\;\mathrm{muscle}\;\mathrm{mass}\;\mathrm{density}\;\left(1,000\;\mathrm{kg}/m^{3}\right)\text{.}$$

Image processing will be converted each pixel of the color map into a shear modulus based on the recorded color scale. Mean shear modulus values will be calculated in a 15 × 15 mm^2^ region of interest in different regions of each muscle fascicular area (38).

The raw EMG signals will be band-pass filtered at 15–500 Hz through a second-order Butterworth digital filter to remove noise or movement interference (39). The data from the different assessments will be collected, rectified, and smoothed using root mean square analysis (RMS) with a 20–ms window (40) calculated using the following equation (36):

$$\sqrt{\frac{1}{T}}\overset{t0+T/2}{\underset{T0-T/2}{\int }}{\left(EMG\right)}^{2}dt,\mathrm{where}\;T\;\mathrm{is}\;\mathrm{the}\;\mathrm{Time}\;\mathrm{of}\;\mathrm{integration}$$

For the MVC assessments, a moving window with a width of 20 ms will be used to find the maximum RMS EMG activity resulting from the three efforts of MVC for each kind of contraction. Then, all RMS EMG data from the different tests will be normalized using the following equation for each muscle:

$$EMG\;RMS\%=\left[\left(RMS\;EMG\;\mathrm{assessment}/RMS\;EMG\;MVC\right)\;x\;100\%\right]\text{.}$$

### Statistical methods

2.8

Statistical analysis will be conducted using Prism 7.0 software (GraphPad Software, Inc., San Diego, United States). The normality of data distribution will be assessed using Kolmogorov–Smirnov tests. If the data follows a normal distribution, the paired t-test (for comparing the same group before and after intervention) and independent t-test (for comparing the control and experimental groups) will be employed. If the data does not follow a normal distribution, the Wilcoxon signed-rank test (paired samples) and the Mann–Whitney U test (independent samples) will be applied. Relationships between different parameters and their variations will be evaluated using Pearson’s correlation analysis. Data will be presented by their means and standard deviations. The chosen significance threshold will be set at *p* < 0.05 for all results.

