### Study design

2.2

This study will be conducted in strict adherence to the Consolidated Standards of Reporting Trials (CONSORT) guidelines, and will employ a single-blinded, controlled, randomized design, wherein participants will be randomly assigned to one of two groups: the conventional therapy group (CTG) or the Eccentric training group (ETG). Both groups will undergo a series of assessments at: Ji (initial assessment) and Jf (final assessment) as illustrated in Figure 1. The study will begin with a recruitment phase, followed by a screening phase. Subsequently, there will be a 4-week period allocated for experimental testing before the intervention, and an additional 4 weeks for experimental testing after the intervention. The experimental testing will include clinical health assessments, biomechanical assessments, neuromuscular evaluations, and functional assessments.

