## Limitations

4

One notable limitation of this study is the heterogeneity within the stroke patient population. Even though participants are in the sub-acute phase, the variability in individual recovery trajectories, severity of stroke, and pre-existing health conditions could lead to significant differences in response to the interventions. This heterogeneity may influence the outcomes and interpretations, making it challenging to draw definitive conclusions that are broadly applicable to all sub-acute stroke patients. We aim to increase the sample size to minimize the effects of data heterogeneity and interpretation bias. Furthermore, this study will focus on penniform muscles. It has been suggested that SWV measurements with small deviations from the fiber direction, as determined by the probe-fascicle angle, may be potentially inaccurate (56). However, previous study on the GM have shown relatively reproducible stiffness measurements (57).

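### Section 2.8 compares the arms with an unadjusted, data-selected test of an undefined quantity and gives within-arm before/after tests equal standing; one baseline-adjusted between-arm model should replace both

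*Protocol article*

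**What the plan says.** The design is a two-arm randomised trial: "participants will be randomly assigned to one of two groups: the conventional therapy group (CTG) or the Eccentric training group (ETG" (section 2.2, Study design). Baseline is measured in everyone: "Both groups will undergo a series of assessments at: Ji (initial assessment) and Jf (final assessment" (same section).

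Section 2.8 (Statistical methods) then fixes the analysis in one paragraph:

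- A normality test comes first: "The normality of data distribution will be assessed using Kolmogorov–Smirnov tests".
- If normality is not rejected, each arm is tested over time by "the paired t-test (for comparing the same group before and after intervention"), and for the arm comparison an "independent t-test (for comparing the control and experimental groups) will be employed".
- If it is rejected, "the Wilcoxon signed-rank test (paired samples) and the Mann–Whitney U test (independent samples) will be applied".
- One threshold applies throughout: "The chosen significance threshold will be set at *p* < 0.05 for all results".

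The section names no covariate and no arm-by-time term. It mentions variations in the parameters only for the correlation analysis, not for the arm comparison. It does not say which of the listed tests supports a claim about eccentric training (ET).

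**The concern.** There are three weaknesses, in descending order of weight.

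First, the randomised comparison is under-defined and unadjusted. The two-sample test could be run on Jf values or on Jf minus Ji. Two analysts following the same text could report different treatment effects with different precision, and neither would use the baseline as efficiently as a model that conditions on it. The Limitations section concedes that "the variability in individual recovery trajectories, severity of stroke, and pre-existing health conditions could lead to significant differences in response to the interventions". In a population that variable, a baseline measurement already in hand is worth using.

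Second, the within-arm tests share the threshold of the randomised comparison. Patients are less than six months post-stroke and both arms receive 12 weeks of active therapy, so improvement in both arms is plausible whether or not ET is superior. A significant paired test in one arm and a non-significant one in the other is not evidence that the arms differ, and nothing in section 2.8 rules out reading it that way.

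Third, the Kolmogorov–Smirnov gate lets the data choose between a difference in means and a rank comparison, outcome by outcome. The quantity being estimated is then not fixed in advance.

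**Working it through.** The article gives no sample size, SD, effect size or Ji–Jf correlation, so there is no figure of the plan's own to reproduce. The inputs below are assumptions: correlation r = 0.6 to 0.8, 20 patients per arm, 1:1 allocation, equal variances, two-sided 0.05.

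**Precision of the between-arm test.** Relative to a t-test on Jf values (variance 1), a change-score test has variance 2(1 − r) and ANCOVA has 1 − r².

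| r | Change score | ANCOVA | Patients needed, Jf-only vs ANCOVA | Patients needed, change vs ANCOVA |
|---|---|---|---|---|
| 0.6 | 0.80 | 0.64 | 1/0.64 = 1.6 | 0.80/0.64 = 1.25 |
| 0.7 | 0.60 | 0.51 | 1/0.51 = 2.0 | 0.60/0.51 = 1.18 |
| 0.8 | 0.40 | 0.36 | 1/0.36 = 2.8 | 0.40/0.36 = 1.11 |

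As an example, take a 0.5 SD effect, r = 0.7 and 20 per arm. Power is 35% on Jf values, 53% on changes and 60% with ANCOVA. For 80% power the numbers per arm are 63, 38 and 33. Below r = 0.5 the change score is worse than the Jf value (at r = 0.3 its variance is 1.40, against 0.91 for ANCOVA), so the choice the text leaves open matters in both directions.

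**Within-arm tests when ET has no effect.** Suppose both arms truly improve by 0.5 SD of the change. With n = 20 the paired t-test has power p = 0.565. The arms are independent, so:

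- ETG significant, CTG not: p(1 − p) = 0.565 × 0.435 = 0.246, about 25%.
- Exactly one arm significant, in either direction: 2 × 0.246 = 0.49. Only half of these cases favour ET, so 25% is the figure for false credit.

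A simulation (20,000 runs per setting, r = 0.7, 20 per arm) with the gain expressed in SDs of the outcome shows how this depends on the size of the common recovery:

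| Common gain (outcome SD) | ETG significant | ETG significant, CTG not |
|---|---|---|
| 0.2 | 20% | 16% |
| 0.3 | 37% | 23% |
| 0.5 | 78% | 17% |
| 0.8 | 99% | 1% |

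The two scales differ: at r = 0.7, 0.5 SD of change is 0.5 × √0.6 = 0.39 outcome SD. Over 15 to 30 per arm and r of 0.7 to 0.8 the discordant result peaks near 25%, which is the maximum of p(1 − p). In the same simulations the between-arm t-test stays at about 5%, on Jf values and on changes alike.

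**The normality gate.** For log-normal data (sigma 0.5) and n = 20, a Kolmogorov–Smirnov test with the Lilliefors correction rejects normality in about 34% of samples, so clear skewness is usually missed. The effect on type I error is small. With the gate applied to either arm and 20 per arm, the two-stage procedure rejects a true null in about 5.7% of trials, against 4.9% for the t-test alone and 5.3% for Mann–Whitney alone.

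**The case against.** The strongest reply is that the trial is randomised and section 2.8 does plan a direct comparison of the arms. Spontaneous recovery is expected equally in both, and the test of the stated objective, ET against conventional therapy, holds its error rate. This stands. A reader might infer that the planned comparison itself credits recovery to ET. It does not, and nowhere does the article say that efficacy will be concluded from significance in one arm only. The risk exists because the paragraph does not say which test is decisive.

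A reader might also infer that the baseline data are wasted outright. That holds only if Jf values are compared. If changes are compared, baseline is used, and the penalty is the smaller one in the first table. The text does not support choosing either reading. Nor does chance baseline imbalance bias a randomised comparison: the standard error already allows for it, and the cost is precision.

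The gate does little harm to type I error, so the objection to it is that the estimand is data-dependent, which is secondary. Baseline adjustment also does not remove the heterogeneity of response described in the Limitations; it removes only the part of outcome variance that baseline predicts.

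Finally, an article may leave detail to a fuller document. But here the tests, the rule for choosing among them and the common threshold are stated, so the point concerns a stated method and not only an omission.

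**Conclusion.** The point holds as a should-fix. The between-arm test in section 2.8 is valid but imprecise and incompletely defined, and the within-arm tests are given a standing that they should not have.

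The precision cost is 1.6 to 2.8 times as many patients if Jf values are compared, or 1.25 to 1.11 times if changes are, for r between 0.6 and 0.8. The risk of false credit to ET is conditional on conclusions being drawn from the within-arm tests. It is then about 25% at 20 per arm and a common gain of 0.5 SD of change, and lower for much smaller or much larger gains. All these figures depend on correlations, sample sizes and gains that the article does not state; they illustrate scale and do not predict this trial's results.

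**What to change.** Rewrite the paragraph in section 2.8 before any between-arm results are seen:

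- For each continuous outcome, pre-specify one linear model of the Jf value on arm and the Ji value. Report the adjusted between-arm difference with its 95% CI, and base every treatment claim on it.
- Remove the Kolmogorov–Smirnov gate. For outcomes expected to be skewed, name in advance a log transform, or a bootstrap or permutation CI for the same model.
- Present within-arm changes descriptively, without p-values.

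The cost is one rewritten paragraph and software that fits ANCOVA; the plan currently names Prism 7.0, so this should be checked. No extra data or visits are needed, because Ji is already collected in both arms.

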Recently, an increasing amount of recent research is focusing on muscle strengthening, particularly eccentric training (ET) (24). ET, a traditional method used to boost muscle strength in athletes, involves muscle contraction during the lengthening of the musculotendinous complex (25). Compared to other training modalities at the same force exertion level, eccentric exercise requires less muscle activity (26). Therefore, this approach could be particularly effective for addressing muscle fascicle shortening and stiffness observed in stroke survivors, due to the increased mechanical load involved during active lengthening (14). This increased load is hypothesized to lead to more significant gains in muscle strength and volume and may also reduce hyperactivity in affected muscles (24). In this context, ET has been demonstrated to enhance muscle strength, reduce spasticity, and improve functional performance and quality of life in chronic stroke survivors following 4 to 6 weeks of intervention (27, 28). As a result, ET offers a myriad of benefits that may be relevant for individuals with neurological conditions (27). However, to our knowledge, no study has investigated the effects of ET on the structural and mechanical properties of the PF, nor on their implications for improving functional capacities. This is particularly relevant given the high prevalence of stiffness in post-stroke patients, which is associated with alterations in the structural and mechanical properties of the muscle-tendon complex, consequently limiting functional capacities (29). These issues are challenging to address in neurorehabilitation, where conventional therapy often fail to produce clinically significant results (30, 31). In fact, conventional therapy, which generally involves stretching exercises, concentric training, and repetitive movements to relearn skills such as balance and locomotion, does not appear to significantly improve the patient’s functional walking abilities beyond 0.04 m/s (32).

The objectives of this study are: (i) investigating the effects of eccentric training on the structural and mechanical properties of PF in stroke survivors compared to conventional therapy, and (ii) analyzing the relationships between changes in structural and mechanical parameters of PF and improvements in walking speed and maximal range of motion.

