## Discussion

3

To the best of our knowledge, this study protocol will be the first to investigate the effects of eccentric training on the structural and mechanical properties of PF in stroke survivors compared to conventional therapy. We hypothesize that a notable distinction will emerge between the two interventions, with the protocol incorporating eccentric strengthening demonstrating favorable outcomes. Moreover, the enhancement in gait speed and ROM will be associated with an improvement in passive and active PF stiffness.

The conceptualized program for this study aims to provide high-intensity training for individuals in sub-acute phase to effectively stimulate various forms of plasticity. The speed, load, and number of repetitions are the factors that form the basis of the eccentric work and upon which its relevance depends. Therefore, these parameters will be considered to achieve the targeted objective. In this context, a recent study conducted by Le Sant et al. (24) has presented compelling evidence that ET significantly enhances motor performance, particularly in terms of maximal strength and power, among individuals within neurological populations. This finding aligns with the observations of Clark and Patten (28) suggesting that the remarkable strength improvements attributed to eccentric training post-stroke may be linked to heightened quadriceps stretch reflex activity. This increased reflex activity supplements the voluntary neural drive during eccentric knee flexion contractions. Conversely, when considering the structural properties of the paretic muscle, (41) calculated the minimum detectable change for the thickness parameter, estimating it to be at 3 mm. Remarkably, these authors observed a noteworthy increase of 3 mm in the thickness of the SOL muscle following a 23-session eccentric training program focused on the PF, but this research was conducted with healthy individuals.

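### Objective (ii) rests on plain Pearson correlation with no arm term or per-arm analysis; if the arms are pooled, a treatment effect on both changes induces a correlation by itself

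*Protocol article*

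**What the plan says.** The Introduction gives two objectives. The second is "analyzing the relationships between changes in structural and mechanical parameters of PF and improvements in walking speed and maximal range of motion". The Discussion attaches a hypothesis to it: "the enhancement in gait speed and ROM will be associated with an improvement in passive and active PF stiffness". The sentence before that states the expected treatment effect, "with the protocol incorporating eccentric strengthening demonstrating favorable outcomes".

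Section 2.8 gives one sentence to this objective: "Relationships between different parameters and their variations will be evaluated using" Pearson's correlation analysis. In that section the comparison of arms appears only in the two-sample tests ("independent t-test (for comparing the control and experimental groups) will be employed", or Mann–Whitney if normality fails). The document describes no partial correlation, regression, arm term or per-arm correlation. Section 2.8 gives a rank alternative for the group tests but none for the correlations. One threshold, p < 0.05, applies to all results.

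**The concern.** Section 2.2 states that "participants will be randomly assigned to one of two groups". If treatment moves two change scores in the same direction, patients in the better arm tend to be high on both and patients in the other arm low on both. A correlation across all patients picks up that separation. It can be clearly positive even when, within each arm, a patient's change in stiffness says nothing about that patient's change in gait speed.

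The artefact therefore grows with the trial's success on its first objective. A finding that eccentric training improves both stiffness and gait would, in pooled data, also tend to look like evidence that the two improvements go together in individual patients. That patient-level link is what objective (ii) asks about and what the Discussion hypothesises.

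**Working it through.** The plan states no sample size, effect size or correlation for this analysis, so there is no figure of its own to reproduce.

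**Inputs from the document**
- Two arms (section 2.2).
- Plain Pearson correlation of parameters and their changes (section 2.8).
- Threshold 0.05 (section 2.8).
- Eccentric arm expected to do better, and gait and range-of-motion gains expected to accompany stiffness gains (Discussion).

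**Assumptions, because the document is silent**
- 1:1 allocation and a two-sided test.
- Total N of 20 to 100.
- Standardised arm effects d1 and d2 on the two changes, from 0 to 1.5 within-arm SD.
- Both changes coded so that improvement is positive.
- Arms pooled, and true within-arm correlation exactly zero.

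**Step 1: induced correlation.** Let a share p of patients be in one arm. Pooling gives covariance p(1−p)·d1·d2 and variances 1 + p(1−p)·d1² and 1 + p(1−p)·d2². Hence

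r = p(1−p)·d1·d2 / √[(1 + p(1−p)·d1²)(1 + p(1−p)·d2²)].

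With p = 0.5 and d1 = d2 = d this becomes r = (d²/4) / (1 + d²/4):
- d = 0.5: 0.0625 / 1.0625 = 0.06
- d = 0.8: 0.16 / 1.16 = 0.14
- d = 1.0: 0.25 / 1.25 = 0.20
- d = 1.5: 0.5625 / 1.5625 = 0.36

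If d1 = 0.8 and d2 = 0, the numerator is zero and r = 0. The artefact needs an arm effect on both variables.

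**Step 2: how often plain Pearson gives p < 0.05.** Results from 20,000 simulated trials per setting:

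| d1, d2 | Induced r | N = 20 | N = 40 | N = 60 | N = 100 |
|---|---|---|---|---|---|
| 0, 0 | 0 | 4.9% | 4.9% | 5.0% | 4.7% |
| 0.8, 0 | 0 | 5.0% | 5.2% | 5.0% | 5.3% |
| 0.5, 0.5 | 0.06 | 5.6% | 6.4% | 7.4% | 9.1% |
| 0.8, 0.8 | 0.14 | 8.6% | 13.4% | 18.2% | 28.2% |
| 1.0, 1.0 | 0.20 | 13.9% | 24.5% | 34.6% | 53.2% |
| 1.5, 1.5 | 0.36 | 38.1% | 67.4% | 85.0% | 97.3% |

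**Step 3: the same data with arm adjusted for.** The partial correlation given arm (each change centred within its arm, N − 3 degrees of freedom instead of N − 2) rejects in 4.7% to 5.3% of trials in every setting tried. That is the nominal rate.

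**The case against.** **Pooling is not stated.** A reader might infer that section 2.8 commits to correlating across both arms. It does not. The paired tests in the same section are within group, and correlations run separately per arm would fit the text and be free of this artefact. An article may also leave covariates to a fuller plan. This stands as far as it goes, so the concern is conditional. But the article does name a method for a stated objective, and as worded that method permits the biased version.

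**Large effects are not supported by the document.** The comparator is active: 36 sessions of isometric and concentric strengthening plus stretching of the same muscles (section 2.5.1). The Discussion calls earlier results of eccentric training on walking mixed. This stands. Effects of 1.0 to 1.5 SD on both variables are the far end of the range, and at 0.5 SD with N = 40 the rate is only 6.4%.

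**A pooled correlation is a real association in the mixed population.** The text speaks of relationships and association, and a reader might infer a planned claim that stiffness change causes gait change. The document makes no such claim for the correlation. Even so, a correlation produced only by the arm difference repeats the result of objective (i) and does not show that the patients whose muscle changes more are those who walk faster.

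**Part of the sentence is unaffected.** Correlations between parameters at baseline carry no treatment effect. The point concerns change-change correlations only.

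**Spontaneous recovery.** A reader might go further and say that recovery in sub-acute patients drives all the changes. The document does not support that. It names variable recovery trajectories as a source of heterogeneity (Limitations) and gives no figure. Recovery may confound the association, but its size is unknown here.

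**Conclusion.** The concern holds in conditional form. Section 2.8 offers only plain Pearson correlation for objective (ii). If the arms are pooled and eccentric training affects both variables, part or all of the correlation reflects the arm difference. The size runs from slight (induced r 0.06 at d = 0.5) to serious (0.36 at d = 1.5), and is nil if only one variable responds to arm. These figures rest on assumed 1:1 allocation, equal effects on both changes, zero within-arm correlation and an assumed N, none of which the document gives. The randomised comparison of the arms is untouched. What is at risk is the second objective and the hypothesis tied to it, which is reason enough to change the wording before analysis.

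**What to change.** In section 2.8, for relationships between changes:
- Replace plain Pearson with a partial correlation or regression that includes arm, and optionally the Ji value. Report the estimate with a 95% confidence interval and show the within-arm results beside it.
- Use a rank-based partial correlation under the same normality rule that the section already applies to its group tests.
- Restrict the main analysis to the hypothesised pairs: passive and active stiffness, each with gait speed and range of motion. Section 2.6.2 measures several muscles, ankle positions and contraction levels, so name in advance which stiffness measures are meant.
- Report the result as exploratory association.

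The cost is one degree of freedom for arm, one more for each further covariate, and slightly more analysis. No new data are needed. Arm adjustment removes only the artefact due to arm. It does not remove confounding by spontaneous recovery, and the report should say so.
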